# Feasibility and Efficacy of Delivering Cognitive Behavioral Therapy Through an Online Psychotherapy Tool for Depression: Protocol for a Randomized Controlled Trial

**DOI:** 10.2196/27489

**Published:** 2021-06-16

**Keywords:** mental health, depression, psychotherapy, cognitive behavioral therapy, online, internet, electronic, virtual, mental health care

## Abstract

**Background:**

Major depressive disorder (MDD) is a prevalent and debilitating mental health disorder. Among different therapeutic approaches (eg, medication and psychotherapy), psychotherapy in the form of cognitive behavioral therapy (CBT) is considered the gold standard treatment for MDD. However, although efficacious, CBT is not readily accessible to many patients in need because of hurdles such as stigma, long wait times, high cost, the large time commitment for health care providers, and cultural or geographic barriers. Electronically delivered cognitive behavioral therapy (e-CBT) can effectively address many of these accessibility barriers.

**Objective:**

This study aims to investigate the efficacy and feasibility of implementing an e-CBT program compared with in-person treatment for MDD. It is hypothesized that the e-CBT program will offer results comparable with those of the in-person treatment program, regarding symptom reduction and quality of life improvement.

**Methods:**

This nonrandomized controlled trial intervention will provide e-CBT for MDD through the Online Psychotherapy Tool, a secure, cloud-based, digital mental health platform. Participants (aged 18-65 years) will be offered 12 weekly sessions of an e-CBT program tailored to MDD to address their depressive symptoms. Participants (n=55) will complete predesigned modules and homework assignments while receiving personalized feedback and interacting with a therapist through the platform. Using clinically validated symptomology questionnaires, the efficacy of the e-CBT program will be compared with that of a group (n=55) receiving in-person CBT. Questionnaires will be completed at baseline, at week 6 and week 12, and at a 6-month follow-up. Focus groups will be conducted to investigate personal, cultural, and social factors impacting the accessibility and feasibility of implementing a web-based psychotherapy tool from a patient and care provider perspective. Inclusion criteria include diagnosis of MDD, competence to consent to participate, ability to speak and read English, and consistent and reliable access to the internet. Exclusion criteria include active psychosis, acute mania, severe alcohol or substance use disorder, and active suicidal or homicidal ideation.

**Results:**

Ethics approval was obtained in January 2019, and recruitment of participants began in June 2019. Recruitment has been conducted via social media, web-based communities, and physician referrals. To date, 52 participants have been recruited to the e-CBT group, and 48 patients have been recruited to the in-person CBT group. Data collection is expected to be completed by March 2021, and analyses are expected to be completed by June 2021, as linear regression (for continuous outcomes) and binomial regression analysis (for categorical outcomes) are still being conducted.

**Conclusions:**

The results of this study can provide valuable information for the development of more accessible and scalable mental health interventions with increased care capacity for MDD, without sacrificing the quality of care.

**Trial Registration:**

ClinicalTrials.gov NCT04478058; http://clinicaltrials.gov/ct2/show/NCT04478058

**International Registered Report Identifier (IRRID):**

DERR1-10.2196/27489

## Introduction

### Background and Rationale

More than 264 million people globally have depression, with major depressive disorder (MDD) being one of the most prevalent mental health disorders [1]. In addition, depression is the largest contributor to global disability and is associated with an estimated economic cost of more than US $2.5 trillion globally [2-6]. Given the large prevalence and the debilitating nature of this mental disorder, discovering effective and accessible treatments for depression is essential and urgently needed.

There are different therapeutic approaches for treating MDD, from medication to psychotherapy. Although pharmacotherapy has been widely investigated and various medications are used to treat MDD, approximately one half of primary care patients only respond partially to medication, with residual symptoms persisting in most cases [7]. Furthermore, many patients using medications for MDD experience adverse effects (eg, weight change, sexual side effects, and sleep problems) or develop addiction or dependency on these medications [8]. These challenges discourage many patients from taking their medications and render this therapeutic path moot as a first-line treatment for MDD.

The current frontline treatment for MDD is in-person psychotherapy, more specifically, cognitive behavioral therapy (CBT) [9-11]. This traditional form of CBT uses a structured format to focus on altering cognitive processing based on the theory that maladaptive behaviors affect an individual’s perceptions, emotions, and thoughts [12]. By altering these maladaptive behaviors, a patient’s thoughts and beliefs can be positively impacted, allowing for a cyclical improvement in cognition and behavior. CBT allows patients to learn the necessary skills to better cope with situations in their lives by better interpreting their thoughts, thereby influencing their emotions. By positively influencing thoughts, mood, behavior, or physical reactions, a positive effect is seen in other areas of one’s life. Through CBT programming, patients can learn skills such as breathing techniques, thought records, activity scheduling, and goal setting, which can give them the tools they need to better control their emotions.

Although CBT is efficacious for treating mood and anxiety disorders, the barriers associated with this treatment make it extremely inaccessible. An effective round of CBT usually requires a large time commitment (ie, 12-15 weekly sessions), making CBT a costly solution for patients. In addition, given the time commitment from the clinicians, there are often extremely long wait times for individuals to receive treatment. Additional barriers to CBT include cultural and language barriers, especially within more culturally diverse countries, geographic isolation in rural areas, and social isolation, particularly in the context of the COVID-19 pandemic. Public stigma, high financial costs, lack of after-hour resources, and confidentiality concerns are also common concerns associated with receiving CBT [13,14]. Therefore, new innovative solutions are needed to make this effective and safe treatment option more accessible to patients in need without sacrificing the quality of care.

Electronically delivered cognitive behavioral therapy (e-CBT) presents itself as a remedy to these barriers. Owing to the structured nature of CBT, it can be effectively delivered remotely in the form of e-CBT. e-CBT offers results comparable with those of the in-person CBT, while increasing treatment adherence and yielding high treatment satisfaction [15,16]. Recent findings have supported the notion of implementing e-CBT for MDD, showing significant improvements in symptoms in various settings [17-19]. The use and accessibility of the internet have continued to grow globally, with more than 40% of the population having access to the internet and more than 2.5 billion individuals currently using the internet [20,21]. Given the increased accessibility to and use of web-based resources, internet-based delivery of mental health treatments can make help accessible and available at any time or place, helping underserved populations, geographically isolated individuals, and people looking for treatment outside of their work hours. In addition, delivering mental health care on the web provides a secure and private environment that could lower the stigma of receiving care, which is particularly useful for patients with MDD who usually show low help-seeking behaviors [22-24]. Furthermore, receiving care on the web allows patients to save time or financial burdens commuting to weekly appointments.

Several forms of e-CBT have been used, including self-help (unguided and self-directed), guided self-help (clinicians provide limited support), and *live* psychotherapy (clinician has the same role as in-person CBT through video conferencing). A meta-analysis [25] revealed that although self-help e-CBT can have varying degrees of efficacy, therapist engagement increases treatment efficacy up to 4 times [26,27]. Therefore, a supervised form of e-CBT is required. Although this supervision can be achieved in *live* psychotherapy through videoconference, the time commitment for clinicians is identical to, if not greater than, that needed for in-person CBT [11]. From this, we can see that an asynchronous form of e-CBT delivery must be used where therapist supervision can be achieved without the strenuous time commitment of in-person CBT. Asynchronous e-CBT has been delivered in previous research; however, these studies used email as the primary method of communication between therapists and patients [28,29]. Although this offers the benefits of therapist engagement, email is an insecure and unsustainable form of patient-clinician communication [30]. This can be achieved by using predesigned and clinically validated therapy content coupled with asynchronous therapist interaction through a secure platform. In doing so, a high standard of care can be achieved without repeating general concepts to all patients, thus saving time.

This study aims to evaluate the efficacy and feasibility of delivering a supervised e-CBT program with streamlined processes for delivering care. By using predesigned therapeutic content, clinicians can skip repeating general concepts across multiple patients and focus on personalizing the treatment. This practice can significantly lower the time commitment from the clinical staff, which lowers the cost of care and increases the capacity, thereby shortening the wait time. Moreover, by validating the therapeutic content and clinical process in this clinical trial, we ensure that a high quality of care is delivered on a routine basis. The predesigned content will be delivered through a secure web-based platform, the Online Psychotherapy Tool (OPTT; OPTT Inc), designed by the lead author. The platform allows clinicians to schedule their interactions and activities with patients, track patient participation, and access analytical tools to improve the quality of care. Clinicians can personalize treatment plans for each patient, similar to *live* psychotherapy, without the time commitment needed for live and face-to-face treatment. By delivering e-CBT for MDD through this web-based platform, the aim is to provide patients with more accessible, affordable, and efficacious treatment options for their problems.

### Objectives

This study aims to implement an e-CBT program to improve symptoms in patients with MDD. This study also aims to deliver this care program through a secure web-based platform structured as a web-based mental health clinic. This e-CBT program will be delivered using a digital care plan (ie, therapeutic content, feedback templates, care procedures, and instructions) specifically designed to address problems faced by patients with MDD. Using qualitative focus groups to collect personal, social, and cultural information from patients and health care providers, the accessibility and feasibility of the program can be better understood.

## Methods

### Study Design

For this study, an open-label, nonrandomized controlled trial study design will be used to compare the efficacy and feasibility of the web-based program with the in-person treatment option in a controlled manner. Blinding will not be possible, as patients will be aware of whether their treatment is occurring in person or remotely. Qualitative focus groups will be conducted with patients to gather personal, social, and cultural factors. These focus groups will be conducted to allow for a natural and open conversation on how participant factors can impact the treatment experience with the program. Additional focus groups will be conducted with therapists to gather information regarding the feasibility of implementing a web-based psychotherapy tool. This will be done to better understand how web-based treatment compares with in-person in terms of usability, time efficiency, and perceived connectedness to patients. These focus groups will occur posttreatment.

Quantitative analyses of e-CBT treatment efficacy will be conducted using standardized and clinically validated symptomology questionnaires. This data collection will occur at baseline, at week 6 and week 12 (posttreatment), and at a 6-month follow-up. In addition, a qualitative analysis of focus group interviews will be conducted with theme extraction. We hypothesize that the e-CBT program will offer results comparable with those of the in-person treatment program regarding symptom reduction and quality of life improvement. On the basis of this design, both the efficacy and feasibility of the e-CBT program can be evaluated and compared with in-person treatment for MDD. All study procedures have been approved by the Queen’s University Health Sciences and Affiliated Teaching Hospitals Research Ethics Board (HSREB; file number 6020045).

### Participants

Patients (N=110; 55 e-CBT participants and 55 in-person CBT participants) aged between 18 and 65 years will be recruited from Queen’s University from the outpatient psychiatry clinic at both the Kingston Health Sciences Center sites (Hotel Dieu Hospital and Kingston General Hospital) as well as from Providence Care Hospital located in Kingston, Ontario, Canada. Additionally, family doctors, physicians, clinicians, and self-referrals will be accepted. Once informed consent is provided, a psychiatrist from the research team will evaluate participants through a secure video appointment to make or confirm a diagnosis of MDD using the Diagnostic and Statistical Manual of Mental Disorders, 5th edition [31].

The inclusion criteria for the study are as follows: aged at least 18 years at the start of the study, diagnosed with MDD according to Diagnostic and Statistical Manual of Mental Disorders, 5th edition by an attending psychiatrist from the research team, competence to consent to participate, ability to speak and read English, and consistent and reliable access to the internet. Exclusion criteria are as follows: active psychosis, acute mania, severe alcohol or substance use disorder, and/or active suicidal or homicidal ideation. If a participant is receiving another form of psychotherapy, they will also be excluded from the study to avoid any confounding effect on the efficacy of this e-CBT program. Participants are eligible for the study if they are receiving pharmacotherapy. However, they must be receiving the same drug and dosage for the duration of the study. If eligible for the study, participants will choose between the e-CBT program (n=55) or the in-person CBT offered individually through this program at Hotel Dieu Hospital (n=55).

During the informed consent process, all participants will be explained that this program is not a crisis resource and that they will not always have access to their therapist. In the case of an emergency, participants will be directed to the proper resources (eg, emergency department or crisis lines), and this event will be reported to the principal investigator of the study. The reasoning behind having a nonrandomized design and allowing patients to choose their treatment is to mimic a real-world setting in which patients have autonomy in their treatment decisions. We recognize that this could be a limitation of this study. We plan to conduct a randomized controlled trial in the future.

### Procedures

The e-CBT care plan consists of 12 weekly sessions of approximately 30 slides and interactive content delivered through OPTT (refer to Multimedia Appendix 1 for the sample module). The e-CBT module content mirrors in-person CBT content, including different weekly topics, general information, skill overviews, and homework. The efficacy of the therapeutic content has previously been tested through email administration and has been shown to reduce depressive symptoms significantly [32]. Participants are instructed to go through the content and complete homework at the end of the session, which helps them practice the skills they learned through that session. Homework is submitted through OPTT and reviewed by the therapist assigned to the participant, who will provide personalized feedback within 3 days of submission. Therapists have access to predesigned session-specific feedback templates to use as a basic structure to write their feedback. By doing so, the time needed to respond to each patient is reduced, and therefore, the number of patients each therapist can handle increases. At the same time, by using a structured format in responding to patients, more standardized quality of care can be ensured. The general structure of the feedback template is as follows: validating the participant’s time and effort, reviewing the event they have used in their homework, summarizing the previous module’s content, and discussing the participant’s homework submission and how they could improve it. In addition to these points, the feedback will emphasize specific content from the participant’s submission, reassuring them that their therapist is reading and understanding their challenges. All feedback submissions are finished with a personalized signature from the therapist, helping to develop a rapport between the therapist and the participant. On average, developing this feedback takes a therapist 15 to 20 minutes per patient. In addition to the weekly feedback, participants have the option to message their therapist through the platform throughout the week regarding any questions or concerns they may have. All technical issues are handled directly by OPTT’s technical support team.

Participants in the in-person CBT group will attend weekly sessions at Hotel Dieu Hospital (12 weeks), where they will receive standardized individual (one-on-one) CBT for MDD from a trained therapist. All content covered and skills taught will mirror the e-CBT program. Similar to the e-CBT group, participants will be assigned weekly homework assignments that they will complete during the week and hand over at the start of their next session. At this time, participants will receive personalized feedback from their therapist for their previous week’s homework.

At the end of the study, a few participants and health care providers (ie, 8 participants and 2 providers) will be recruited for focus groups. The focus group prompts will pertain to experience and expectations of service during the study and how they think the service could be improved.

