### Training

All therapists are research assistants hired by the principal investigator. All therapists undergo training in psychotherapy and receive additional training from a psychiatrist from the research team before any interaction with participants. During this training, therapists complete feedback on practice homework, which is reviewed by a psychiatrist from the research team to ensure adequate quality of work. All therapists are supervised by the lead psychiatrist, who is an expert in electronically delivered psychotherapy [23,24]. Feedback is always reviewed by the lead psychiatrist, before submission to the participants.

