### Data Analysis

This is a confirmatory study with previously established objectives and analyses. Initially, all data are examined for missing, nonsensical, and outlying variables. Missing data are treated as missing and not imputed (ie, will be analyzed on a per-protocol basis). The participants in this study were intentionally oversampled to account for dropouts or withdrawals. On the basis of previous research, an anticipated dropout rate of up to 30% was factored in. Using the PHQ-9 as the primary outcome, a 30% change is considered clinically significant. Therefore, a sample size of 55 participants in each arm of the study would be sufficient for detecting significant results with *P*=.05 and a power of 0.95. Data collection occurs at baseline (preintervention), in the middle of the study (week 6), immediately after the intervention (week 12), and at a 6-month follow-up. Using Mann-Whitney *U* tests, demographic information can be compared between participants who complete the program and those who withdraw prematurely in the hope of identifying possible differences between the two. Moreover, an intention-to-treat analysis will be conducted to evaluate the clinical effects of treatment on participants who withdraw prematurely. Linear regression analysis (for continuous outcomes) and binomial regression analysis (for categorical outcomes) will be used to identify variables associated with the outcome measures (PHQ-9, Quick Inventory of Depressive Symptomatology Questionnaire, and Quality of Life and Enjoyment Questionnaire). This will occur over the 4 measurement time points while controlling for demographic variables, including age and gender. In addition, a comparative analysis between both groups’ questionnaire scores will be conducted at all data collection time points using group and paired two-tailed *t* tests.

Other quantitative measures for the e-CBT group will be gathered by extrapolating recorded information directly through the OPTT platform (eg, the number of log-ins per day and the amount of time spent logged in). Qualitative measurement analyses will be conducted to inquire about the role of personal, social, and cultural factors in enabling or constraining the use of e-CBT. The findings will identify factors related to the utility, feasibility, and accessibility of e-CBT from the perspectives of users and providers. Interpretive qualitative methods are ideal for gathering in-depth descriptions of user experience and meaning.

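### The named arm comparisons treat participants as independent although they share therapists; if therapists are nested in arm, the standard errors are too small

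*Protocol article*

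**What the plan says.** **Delivery.** Under Procedures, the e-CBT arm works through an assigned therapist: "Homework is submitted through OPTT and reviewed by the therapist assigned to the participant". For the in-person arm, "they will receive standardized individual (one-on-one) CBT for MDD from a trained therapist". That each in-person participant keeps one therapist throughout is implied by the description of feedback in that section, not stated outright. Therapists carry more than one patient: Procedures says that with feedback templates "the number of patients each therapist can handle increases". Training describes a single pool: "All therapists are research assistants hired by the principal investigator".

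**Analysis.** Data Analysis calls the study confirmatory and fixes the arm comparison: "a comparative analysis between both groups’ questionnaire scores will be conducted at all data collection time points using group and paired two-tailed *t* tests". It also plans linear and binomial regressions, of which it says: "This will occur over the 4 measurement time points while controlling for demographic variables, including age and gender". No therapist term, cluster-robust error or design effect is named there or in the sample-size statement.

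**Not given.** The article does not state how many therapists there are, their caseloads, an ICC, or whether a therapist works in one arm or in both.

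**The concern.** Participants treated by the same therapist tend to have outcomes more alike than participants of different therapists. A two-sample t test ignores this. If each therapist works in one arm only, differences between therapists add to the variance of the arm difference, and the t test does not count that extra variance. Its interval is then too narrow and its p-value too small.

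The study's hypothesis is that e-CBT gives results comparable with in-person CBT. An interval that is too narrow would make a conclusion about comparability, or about a difference, look firmer than the data allow. If instead the same therapists treat both arms, their effects largely cancel in the arm difference, and leaving them out wastes precision. Either way, the named test does not match the delivery that the article describes.

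**Working it through.** **1. The plan's own figure.** Data Analysis states 55 per arm, P=.05, power 0.95, a 30% PHQ-9 change and up to 30% dropout. It gives no SD or baseline mean, so 55 can be neither confirmed nor refuted. Solving backwards with n = 2(1.96 + 1.645)²/d²:
- All 55 analysed: d = 0.69 gives 2 × 13.0/0.476 = 54.6, so 55.
- With dropout: d = 0.83 gives 2 × 13.0/0.689 = 37.7, so 38, and 38/0.70 = 54.3, so 55.

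Neither route contains an allowance for clustering.

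**2. Therapists nested in arm.** Assumptions, not in the article: 2 to 10 therapists per arm, equal caseloads, ICC 0.01 to 0.10. Formulas:
- caseload m = participants per arm / therapists per arm
- design effect DE = 1 + (m − 1) × ICC
- true SE = naive SE × √DE
- true two-sided error of a nominal 5% test = 2 × (1 − Φ(1.96/√DE))

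With 55 analysed per arm (each cell is DE, then true error):

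| Therapists per arm | m | ICC 0.01 | ICC 0.02 | ICC 0.05 | ICC 0.10 |
|---|---|---|---|---|---|
| 2 | 27.5 | 1.265; 0.081 | 1.53; 0.113 | 2.325; 0.199 | 3.65; 0.305 |
| 3 | 18.3 | 1.173; 0.070 | 1.347; 0.091 | 1.867; 0.151 | 2.733; 0.236 |
| 5 | 11 | 1.10; 0.062 | 1.20; 0.074 | 1.50; 0.110 | 2.00; 0.166 |
| 10 | 5.5 | 1.045; 0.055 | 1.09; 0.060 | 1.225; 0.077 | 1.45; 0.104 |

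Mid case, 5 therapists per arm and ICC 0.05: DE = 1 + 10 × 0.05 = 1.50 and √1.50 = 1.22. Then 1.96/1.22 = 1.60, and the error is 0.11. The effective size is 55/1.50 = 36.7 per arm. At d = 0.69, power with the correct standard error is about 0.84 instead of 0.95. Restoring 0.95 would need 55 × 1.50 = 82.5, so 83 analysed per arm.

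**3. The same mid case after 30% dropout.** 55 × 0.70 = 38.5 per arm and m = 38.5/5 = 7.7. DE = 1 + 6.7 × 0.05 = 1.335, √DE = 1.155, and the error is 0.09.

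**4. The same therapists serving both arms evenly.** The therapist main effect cancels, so the true SE is √(1 − ICC) times the naive SE. For ICC 0.01, 0.05 and 0.10 the ratio is 0.995, 0.975 and 0.949, and the true error is 0.049, 0.044 and 0.039. The t test is then slightly conservative.

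**5. Limit of the approximation.** These figures use the normal distribution and ignore the few degrees of freedom that therapists supply. With 2 or 3 therapists per arm, the loss in a correct analysis would be larger than shown.

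**The case against.** The strongest objection is that the article does not show the condition that does the harm. It gives no therapist numbers, ICC or allocation, and one pool of research assistants is compatible with therapists serving both arms. A reader might infer that therapist differences are mixed into the arm effect and that the error bars are certainly wrong. The documents do not support that: under even crossing the error is at or below 5%, so even the direction is unknown. This part of the objection stands, and the point is therefore stated conditionally. Nor does it follow that a strong or weak therapist cannot be told apart from the arm effect. That is literally so only with one therapist per arm.

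Second, the delivery is standardised. Content mirrors across arms, templates structure the feedback, all therapists are trained and supervised, and "Feedback is always reviewed by the lead psychiatrist, before submission to the participants". This makes a small ICC plausible, and with 10 therapists per arm and ICC 0.01 the error is only 0.055. But templates and prior review apply to written feedback, and no equivalent review before delivery is described for in-person sessions. The article does not show that the ICC is small.

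A reader might go on to infer that therapist skill varies most in the in-person arm, because the training exercise described is written feedback. That is not supported: Training also gives every therapist psychotherapy training and supervision by the lead psychiatrist.

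Third, therapist numbers and model details are commonly left to a full protocol or SAP. That is fair for those details, and their absence is not the point. The point is that the article itself names t tests that assume independence.

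Fourth, participants choose their arm, which the article acknowledges as a limitation. That may well be the larger threat, and a therapist term does not cure it. It also means that balanced caseloads across arms cannot be assumed.

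**Conclusion.** The concern holds in conditional form. The named comparisons assume an independence that the described delivery does not provide. If therapists are nested in arm, the standard errors are too small by a factor of about 1.02 to 1.91 (√1.045 to √3.65) over the assumed range, and a 5% test has a true error of about 0.055 to 0.31. The mid case is 0.11, or 0.09 after 30% dropout. If the same therapists serve both arms evenly, the test is slightly conservative (0.039 to 0.049) and gives up some precision. Uneven sharing would fall between these two cases.

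All these sizes rest on assumed therapist numbers, caseloads and ICC. At the favourable end the effect is negligible. The change is still worth making before the arms are compared, because it is cheap and corrects the interval in whichever direction is needed.

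**What to change.** Attach a coded therapist ID to every participant in both arms. Compare arms with a model of the score on arm that includes therapist:
- If therapists are nested in arm, use a random therapist effect with a small-sample correction to the degrees of freedom.
- If therapists cross arms, use a fixed or random therapist term.

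At minimum, pre-specify this as a sensitivity analysis to the t test. Report the number of therapists, their caseloads and their outcomes by arm, and say whether any therapist worked in both.

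**Cost.** One variable and a change of analysis wording, with no further data from participants. The article does not say that the in-person therapist's identity is already recorded, so it may have to be retrieved. If therapists are nested in arm, the interval widens. If they are few, the therapist variance is estimated imprecisely, and the report should say so. Reassigning therapists across arms is not proposed: 52 + 48 = 100 of the 110 participants were already recruited, so the remedy lies in the analysis.
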